### Statistical analysis

Statistical analysis will be performed using IBM SPSS Statistics 25 (http://www.spss.com.hk). Intention-to-treat (ITT) analysis will be used to analyze the result which means the last observation will be used for interpolation when data missing. Continuous variables will be described as mean ± SD for normal distributions, or median and inter-quartile ranges for non-normal distributions, while categorical variables will be described as frequency. For continuous variables that meet the assumptions of a normal distribution and homogeneity of variance, we will use the Two-way of variance with repeated measures; the Wilcoxon test will be used if not. A chi-square test will be used for categorical variables. Pearson correlation coefficient will be performed to detect the correlation between the primary outcomes (VAS, TQPEAK) and secondary outcomes (MEP, FC). When analyzing data obtained by repeated measurements, we will use two-tailed multivariate analysis of variance. The results will be considered statistically significant when the P value is less than 0.05. The post hoc comparisons will be performed by the Bonferroni correction for multiple comparisons if necessary.

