## Background

Knee osteoarthritis (KOA) is a chronic degenerative joint disease characterized by degenerative cartilage lesions and secondary bone hyperplasia of the knee joint [1]. KOA accounts for more than 80% of total osteoarthritis and is the leading cause of disability, decrease quality of life in the adult and elderly population [2]. The management of KOA may be requiring long-term treatment, leading to significant financial strain on individuals, families, and society as a whole. Consequently, it is imperative to investigate and find effective therapeutic approaches for individuals with KOA, benefiting both the affected individuals and society at large.

To date, there is no proven treatment method that can reverse the course of KOA [3]. Current therapeutic strategies for KOA are focus on improving muscle strength or relieving pain, including medication, physical exercise, intra-articular injection, etc. Clinical guidelines recommend physical exercise as one of the most critical non-pharmacological treatments of KOA [4], which has been proven to improve knee function effectively [5]. Quadriceps strengthening is an critical component of the exercise program because it has been found that patients with KOA always have significant quadriceps weakness [6]. Previous studies indicate quadriceps strengthening is benefit for the relief of knee joint pain and stiffness and improving quality of life [7–9]. Although exercise is effective in KOA, a recent meta-analysis indicated its treatment benefits are moderate for pain and function, performance at or nearest to 8 weeks. Besides, the exercise effects appeared to peak around 2 months and then gradually decreased and became no better than usual care after 9 months [10]. It means the effects of exercise will plateau and pain always persist. Leandro et al. [11] also have proved that exercise treatment effectiveness and adherence seem to decrease over time.

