### Sample size calculation

The sample size was determined based on the priori power analysis through G*Power software version 3.1.9.2. OMERACT-OARSI hip and knee osteoarthritis core outcome set [23] showed that the pain is the most core outcome and the percentage frequency is 94.8% from 1997 to 2017. Furthermore, Guinot et al. [24] reported that the effect size of rTMS for improve pain score in patients with fibromyalgia was 0.24. Therefore, the effect size was set as 0.24 in the present protocol. In the calculations, ANOVA repeated measures between factor was chosen, effect size 0.24, alpha 0.05, power 0.80, number of groups 4, number of measures 6, and the sample size was calculated as 116. Taking into account a conservative anticipation of a 20% drop-out rate, the final sample size will therefore be 37 in each group, with a total of 148 subjects.

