### Recruitment, enrollment and randomization procedures

All patients with KOA will be recruited from the orthopedics or joint surgery department of Shanghai Seventh People’s Hospital in China and communities around the hospital. Recruitment methods will include posters, online advertisements, and leaflets. We will communicate with prospective participants about the study details. After the patients voluntarily sign the informed consent, they will be invited to participate in the study. Recruitment will start from 1 October 2023, until when 148 participants are enrolled.

A total of 148 eligible participants will be assigned to four groups at a 1:1:1:1 ratio using stratified randomization with gender, age and KL grade as factors in this research. The stratified randomization will be achieved as follows: Firstly, participants will be invaded into men and women two groups. Secondly, the two groups will be grouped by age (< 50 and ≥ 50). Lastly, the four groups will be grouped by KL grade (II and III), a total of 8 subgroups. In these eight subgroups, the subjects will be randomly regrouped the QT group, HT group, ST + Q group and HT + Q group. Finally, all four groups will be regrouped into four new groups to minimize the bias of the final results. The randomization procedure is performed by an independent research assistant who is not comes into contact with the participant at any point prior to randomization and is not involved in the data collection using Microsoft Excel to generate the random number (https://www.microsoft.com).

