### Interventions

All participants will receive usual care management, including health education and physical therapy when necessary. Six qualified physiotherapists who have attained the physical therapist’s certification with over 5 years of experience will be trained beforehand to instruct and guide patients in carrying out these exercises. The interventions in four groups will be carried out 5 days per week for a total of 12 weeks.

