### Effectiveness

#### Primary outcomes: VAS

The Visual Analog Scale (VAS) will be used as one of the primary outcomes to evaluate the improvement of knee pain, which consists of a 10-cm line, where 0 represents “no pain” and 10 represents “worst possible pain”. The participants will be asked to recall knee pain related to knee joint movement in the previous week and mark on the line. The reliability and validity of the VAS in application of musculoskeletal conditions is proved good [35]. In order to determine the clinical significance of the change in VAS score, the minimal clinically important difference (MCID) will be employed, and the MCID set as 1.16 based on previous study [36].

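### The protocol defines intention-to-treat as last observation carried forward and states no other missing-data rule for 12-week VAS pain; this can bias the comparison in either direction

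*Protocol article*

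**What the plan says.** Under Statistical analysis the article states: "Intention-to-treat (ITT) analysis will be used to analyze the result which means the last observation will be used for interpolation when data missing". It names no other way of handling missing data. The main analysis there is a two-way repeated-measures analysis of variance.

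The rule reaches the primary result. Under Primary outcomes: VAS: "The Visual Analog Scale (VAS) will be used as one of the primary outcomes to evaluate the improvement of knee pain". The Outcomes section sets the primary end-point at 12 weeks.

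Missing data are expected. The Sample size calculation section inflates the number, "Taking into account a conservative anticipation of a 20% drop-out rate". The Drop-out criteria section lists three routes out: not being able to come back for treatment, whatever the cause; adverse events caused by treatment; and receiving other treatment for knee osteoarthritis or anything else that may disturb the results, with corticosteroids, knee surgery and regular exercise among the examples.

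**The concern.** Two separate ideas have been merged. Intention-to-treat is a rule about the analysis set: everyone randomised, in the group to which they were allocated. It does not say what value stands in for an outcome that was not observed. LOCF does say that, and its answer is that pain at week 12 equals pain at the last visit attended.

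That answer matters here because the listed reasons for drop-out are not obviously unrelated to outcome or arm. Someone who seeks another treatment may be in more pain, and adverse events may differ between arms with and without active rTMS. Patients also know their allocation (Allocation concealment and blinding). If the arms lose different numbers, or are changing at different speeds when people leave, the carried values shift the arm means by different amounts. The repeated-measures analysis then treats those values as if they had been measured. At stake is the week-12 VAS comparison on which the trial will be judged.

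**Working it through.** **1. The plan's own figure.** The inputs are "effect size 0.24, alpha 0.05, power 0.80, number of groups 4, number of measures 6, and the sample size was calculated as 116". The within-person correlation ρ is not given; 0.5 is assumed. For the between-groups test in repeated measures:

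λ = f²·N·m / [1 + (m − 1)ρ] = 0.0576 × 116 × 6 / 3.5 = 11.45, with 3 and 112 degrees of freedom, gives power 0.806.

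So 116 is reproduced (ρ = 0.3 would give 84, and ρ = 0.7 would give 148, before drop-out). Per group, 29 / (1 − 0.20) = 36.25, rounded up to 37, and 4 × 37 = 148. This matches: "the final sample size will therefore be 37 in each group, with a total of 148 subjects". The sample size is not in question.

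**2. How many values are exposed.** 0.20 × 37 = 7.4 per arm, about 30 of 148 overall. The article does not tie the 20% to a visit, so fewer may be missing at week 12.

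**3. Expected LOCF difference.** For an arm with drop-out proportion d, the LOCF mean change is (1 − d)·μ12 + d·μlast. The article gives no arm means, no VAS standard deviation and no drop-out by arm, so these values are assumptions: arm A changes by −2.5 cm at week 12 and −1.0 at week 4, arm B by −1.3 and −0.8, and drop-outs leave after week 4 but would otherwise have followed the completers. The true difference is 1.2 cm.

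| Loss A v B | LOCF mean A | LOCF mean B | Difference |
|---|---|---|---|
| 20% v 20% | 0.8(−2.5) + 0.2(−1.0) = −2.20 | 0.8(−1.3) + 0.2(−0.8) = −1.20 | 1.0 |
| 30% v 10% | 0.7(−2.5) + 0.3(−1.0) = −2.05 | 0.9(−1.3) + 0.1(−0.8) = −1.25 | 0.8 |
| 10% v 30% | 0.9(−2.5) + 0.1(−1.0) = −2.35 | 0.7(−1.3) + 0.3(−0.8) = −1.15 | 1.2 |

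Put generally, the understatement is 1.5·dA − 0.5·dB. It is zero in the last row only because dB is exactly three times dA.

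**4. A second set of assumed means.** Improvements of 3.16 v 2.0 at week 12 (true difference 1.16), reached in a straight line, with the week-4 value carried (one third of the final change): LOCF gives 1.01 at 20% v 20%, 0.66 at 30% v 10%, and 1.35 at 10% v 30%. The last is an overstatement.

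**5. Drop-out related to outcome.** Same means, but drop-outs are really back at baseline pain by week 12, with 30% v 10% loss. Truth: 0.7 × 3.16 − 0.9 × 2.0 = 0.41. LOCF gives 0.66 (week-4 value carried) or 0.91 (week-8 value carried), again too large.

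**6. No true difference.** Simulation: 37 per arm, both arms improve by 2.5 in a straight line, SD 2, correlation 0.5, drop-out at random with the last visit equally likely to be baseline, week 4 or week 8, t-test at week 12, nominal 5%.

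| Loss | Type I error under LOCF |
|---|---|
| 20% v 20% | 4.7% |
| 25% v 15% | 6.2% |
| 30% v 10% | 9.7% |
| 40% v 0% | 27% |

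The spurious shift at 30% v 10% can be checked by hand: carried values miss on average two thirds of the change, so (0.30 − 0.10) × (2/3) × 2.5 = 0.33 cm; the simulation gave 0.34.

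**The case against.** The best defence is that none of the bias figures comes from the article. Unequal loss is assumed, and the outcome depends on which arm loses more: with the first set of means, 10% v 30% leaves the difference untouched. With equal loss and no true effect there is essentially no bias, and type I error stays near 5%. All of that stands. It limits what can be said about size and direction, but it does not support LOCF, whose adequacy depends on a drop-out pattern that nobody can know in advance.

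Several stronger readings are tempting and are not supported:

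- *LOCF must overstate durability at 6 months.* The Background says "the exercise effects appeared to peak around 2 months and then gradually decreased and became no better than usual care after 9 months", but that concerns exercise against usual care, not the contrast between the combination and training alone. The result also depends on when people leave. If a true difference has faded to 0.3, carrying a week-12 difference of 1.2 for 20% gives 0.8 × 0.3 + 0.2 × 1.2 = 0.48, while carrying a week-4 difference of 0.2 gives 0.28. Six months is not the primary end-point either.
- *The drop-out criteria contradict usual care.* The Interventions section says "All participants will receive usual care management, including health education and physical therapy when necessary". The criterion on other interventions reads naturally as treatment from outside the trial, so no contradiction is shown.
- *Even a trivial adverse event removes a participant, and assessment then stops.* The criterion gives no grade, and the article does not say that assessments end at drop-out.
- *Single imputation makes the standard errors too small here.* The equal-loss simulation shows no inflation; the inflation seen comes from bias under unequal loss.

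It may also be said that missing-data detail belongs in a fuller document. That would excuse silence, but the article is not silent: it fixes the rule.

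**Conclusion.** The point holds in a limited form. The article wrongly defines intention-to-treat as LOCF and makes LOCF the only stated missing-data rule for week-12 VAS. With 20% drop-out anticipated, for reasons that may be related to pain or arm, the rule can bias the primary comparison in either direction.

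Size and direction cannot be fixed from the document. Under the assumptions shown, a true difference of about 1.2 cm is estimated at anything from 0.66 to 1.35 when week-4 values are carried, and type I error ranges from about 5% with equal loss to about 10% at 30% v 10%. These are illustrations and not estimates for this trial. A reader might infer that LOCF will hide a benefit, or push it below the stated VAS MCID of 1.16; neither follows. The assumed true difference lies only 0.04 above that figure, and the article applies the MCID to change in VAS without making it a threshold for the difference between arm means.

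**What to change.** 1. Define intention-to-treat as all randomised participants analysed in their allocated group, and remove the link to imputation.
2. Replace LOCF with a likelihood-based mixed model for repeated measures using all observed visits, with the arm contrast at week 12 as the primary estimate. The named software can fit it.
3. State that meeting a drop-out criterion does not end outcome assessment: VAS continues to be collected at the scheduled visits, the event is recorded, and the data are included. This step is essential. In step 5 of the working, a mixed model on pre-drop-out data alone would aim at about 1.16 against a truth of 0.41, so changing the model does not by itself cure outcome-related loss.
4. Add a delta-adjusted multiple-imputation sensitivity analysis for informative drop-out, allowing different shifts by arm.

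Decisions on stopping treatment are unaffected and N = 148 stands. The cost is a change of wording, some extra follow-up contacts for people who stop treatment, and a modest amount of analysis work. Step 3 should come early, because VAS scores not collected after drop-out cannot be recovered later.

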## Methods

### Study design

This study will be a randomized controlled trial with a parallel-group design. A total of 148 eligible participants will be assigned to the quadriceps strength training (QT group); high frequency rTMS (HT group); sham rTMS and quadriceps strength training (ST + Q group); high frequency rTMS and quadriceps strength training (HT + Q group) at 1:1:1:1 ratio using stratified randomization with gender, age and Kellgren-Lawrence (KL) grade as factors. A brief flowchart of the entire study is shown in Fig. 1 and the schedule of events is provided in Table 1. The study protocol was approved by the Ethics Committee of Shanghai Seventh People’s Hospital (2022-7th-HIRB-065) and registered in the Chinese Clinical Trial Registry (ChiCTR2300067617).

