### Outcomes

Participants will be assessed by other physiotherapists blinded to the group allocation at different time points based on different assessments shown in Table 1. Additionally, baseline age, gender, symptoms, disease severity, duration, previous treatment and medication will be recorded using a questionnaire (in week 0). The primary end-point is the 12 weeks and all side effects during the study also will be recorded in real time.

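### Two methods are assigned to the repeated pain scores without precedence, the Wilcoxon fallback cannot serve a four-arm repeated design, and no named test directly targets HT+Q versus quadriceps training at week 12

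*Protocol article*

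**What the plan says.** All places are in the protocol article.

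- **Statistical analysis, first rule.** Continuous variables that satisfy normality and equal variance go to a repeated-measures analysis, and the rest to a rank test: "we will use the Two-way of variance with repeated measures; the Wilcoxon test will be used if not".
- **Statistical analysis, second rule.** "When analyzing data obtained by repeated measurements, we will use two-tailed multivariate analysis of variance". Nothing links this to the first rule or ranks the two.
- **Statistical analysis, pairwise tests.** Bonferroni-corrected post hoc comparisons are made only if needed. No pair of arms and no visit is named.
- **Abstract.** Only the two-way repeated-measures analysis appears, for group and time effects. The visits listed are baseline, three during treatment and three in follow-up.
- **Outcomes.** "The primary end-point is the 12 weeks". VAS, a continuous 10-cm scale, is a primary outcome.
- **Background.** The question is whether HT+Q does better than quadriceps training alone.
- **Sample size calculation.** "ANOVA repeated measures between factor was chosen", with "effect size 0.24, alpha 0.05, power 0.80, number of groups 4, number of measures 6, and the sample size was calculated as 116".
- **Study design.** Allocation is made "using stratified randomization with gender, age and Kellgren-Lawrence (KL) grade as factors".

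**The concern.** Three defects lie in what the section states, not in detail that it leaves out.

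1. **Two rules cover the same data.** VAS is continuous and repeatedly measured, so it meets the condition of both sentences. Univariate and multivariate tests of repeated data can give different P values, and the text does not say which one decides.
2. **The fallback does not fit the design.** A rank-sum test compares two samples and a signed-rank test compares two paired occasions. Neither handles four arms over several visits. The switch depends on assumption checks on the trial's own data, with no criterion given.
3. **The target is missed.** The end-point is week 12 and the question concerns two treatment strategies. The group effect pools visits and tests any difference among four arms. A significant result would not show that HT+Q beats quadriceps training at week 12, and a non-significant one would not rule it out.

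At stake is whether the trial's main conclusion rests on one estimate fixed in advance or on a choice made after the data are seen.

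**Working it through.** **Step 1. Which rule applies to VAS?**

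| Feature of VAS | Rule triggered |
|---|---|
| Continuous, assumptions met | Two-way repeated-measures ANOVA |
| Continuous, assumptions not met | Wilcoxon test |
| Obtained by repeated measurement | MANOVA |

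The third row always applies, together with one of the first two. No sentence resolves the overlap.

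**Step 2. What can the fallback deliver?** Four arms give 4 × 3 / 2 = 6 pairs. Pairwise Wilcoxon tests are possible, at 0.05 / 6 = 0.0083 each under Bonferroni, but the plan names no pairs, visit or correction for them. Even then they would give no omnibus or group-by-time result.

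**Step 3. Reproduce the sample size.** Inputs from the Sample size calculation section: f = 0.24, alpha 0.05, k = 4 groups, m = 6 measures, N = 116. The correlation between measures, ρ, is not stated; assume 0.5. For the between factor:

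λ = f² N m / [1 + (m − 1)ρ] = 0.0576 × 116 × 6 / 3.5 = 11.45, with 3 and 112 df.

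Power is 0.806. In equal groups, N = 112 gives 0.790, so 116 is the smallest N that reaches 0.80. Dropout: 29 / 0.80 = 36.25, rounded up to 37; 37 × 4 = 148. Both stated figures reproduce. With m = 7 and ρ = 0.5 the answer is still 116.

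The arithmetic is therefore sound, but it belongs to a test averaged over visits and across all four arms.

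**Step 4. Compare with a week-12 test.** Assume that f = 0.24 holds at week 12 alone and that r is the correlation of baseline with week-12 VAS (not in the document). Adjusting for baseline gives λ = f² N / (1 − r²) with 3 and 111 df; the strata are not modelled. For simplicity ρ and r take the same value.

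| Assumed correlation | Sized test: six visits averaged, N = 116 | Baseline-adjusted week-12 four-arm test, N = 116 | Evaluable N for 0.80 at week 12 |
|---|---|---|---|
| 0.3 | λ = 16.04, power 0.93 | λ = 7.34, power 0.60 | 180 |
| 0.5 | λ = 11.45, power 0.81 | λ = 8.91, power 0.69 | 148 |
| 0.7 | λ = 8.91, power 0.69 | λ = 13.10, power 0.86 | 104 |

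Without baseline adjustment, λ = 0.0576 × 116 = 6.68, power is 0.55 and 196 evaluable patients are needed.

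**Step 5. From four arms to one pair.** f does not fix any pairwise difference. If two arms sit at each of two levels, the largest standardised difference is 2f = 0.48. If two arms sit at the extremes and two at the midpoint, it is √8 × f = 0.68. HT+Q versus QT need not be the largest difference. The power of the contrast of interest therefore cannot be read from the plan.

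**The case against.** **The MANOVA sentence may mean the multivariate tests of the same repeated-measures model.** That is plausible: the abstract names only one method and the sample size rests on it. A reader might infer that two rival primary P values are certain, and the text does not establish that. It does leave the deciding test unstated on either reading.

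**Covariates are normally left to a statistical analysis plan.** This stands. The article does not say that baseline VAS or the strata will be left out, and its silence is no error. They enter here only because the primary analysis has to be rewritten anyway.

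**The planned test is not simply weaker.** This also stands, and three tempting readings fail.

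- A reader might infer that a null baseline visit dilutes the effect by one seventh. That needs baseline to be one of seven outcome levels. The Sample size calculation section counts six measures, which matches the six post-baseline visits, and the schedule table is not shown. If baseline were included, the effect would be 6/7 × 0.24 and power 0.67 at correlation 0.5.
- A reader might infer that baseline adjustment at week 12 must raise power. The Step 4 table shows that the direction depends on an unstated correlation. An unadjusted week-12 t-test is no fair benchmark, because it is not the planned analysis.
- A reader might infer that averaging over follow-up dilutes a fading effect. The Background describes exercise fading relative to usual care. HT+Q and both quadriceps comparators include the exercise, and nothing is said about the durability of the added rTMS effect.

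**Post hoc tests could supply the contrast.** They could, but they are optional and name neither pair nor visit.

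**Conclusion.** The point holds for the stated rules. VAS is covered by two methods without precedence. The Wilcoxon fallback cannot answer a four-arm or group-by-time question. The sized group effect is not the week-12 comparison of HT+Q with quadriceps training. These conclusions follow from the text and need no assumed figure.

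The effect on power is uncertain in size and direction. Relative to the sized test, moving to an adjusted week-12 four-arm test changes power from 0.93 to 0.60, from 0.81 to 0.69, or from 0.69 to 0.86 at assumed correlations of 0.3, 0.5 and 0.7. This takes f = 0.24 as constant over visits, 116 evaluable patients and equal values of the two correlations. At 0.5, the value that reproduces the plan's own 116, the week-12 test falls short of the stated 0.80. The case for change is therefore that the analysis should answer the stated question with one prespecified estimate, not that it gains power.

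**What to change.** 1. Name one primary analysis: a linear mixed model of observed post-baseline VAS with arm, visit, arm-by-visit, baseline VAS, sex, age group (below 50, 50 and over) and KL grade. Feed it observed values only; the last-observation carry-forward in the current text should not supply values to this model.
2. Report the week-12 contrast of HT+Q with quadriceps training and its 95% CI: against QT, the comparator in the stated objective, and against ST+Q, to isolate active stimulation. Fix the order in advance. Which comes first is the sponsor's choice; the documents do not make ST+Q primary.
3. Use the same model for the other repeatedly measured continuous outcomes, so that none is left without an analysis. If residuals are skewed, take bootstrap intervals from the same model.
4. Delete the MANOVA sentence and the Wilcoxon fallback.
5. Restate power for the chosen week-12 contrast, with the assumed correlation and a range.

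**Cost.** Items 1 to 4 need wording and modest programming, with no new visits or data. The real downside is item 5: power for the chosen contrast may fall below 0.80 with 148 randomised, and the sponsor would then have to accept that openly or revisit the sample size. The change should be made before anyone sees unblinded data.

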## Discussion

KOA is classified as a peripheral joint disease, but changes in sensation-movement and pain are mediated by the central nervous system. Rasch et al.[53]proved that the muscle weakness caused by osteoarthritis is related to decreased joint function and increased pain, and that quadriceps training can increase muscle strength and relieve joint pain. Patients with KOA often exhibit strength deficiencies [1] and altered neuromuscular control [54] compared to those without KOA, which may result in suboptimal load dissipation within the knee. Though the motor output and pain changes resulting from KOA have been well-studied, the central contribution to muscle activity is less well known. In this protocol, we design four groups to prove the therapeutic role of high-frequency rTMS combined with quadriceps strength training compared to quadriceps strengthen training alone in KOA patients with 12-week intervention and explore changes of brain volume and function connection before and after treatment.

There are only two studies to prove the treatment effect when combined noninvasive brain stimulation (tDCS) with exercise has been publicized [55, 56]. However, the design of the trial was inadequate, which used inappropriate randomization procedures had a small sample size. And the evaluation is only limited to the change of pain in KOA. Thus, we designed a stricter study to explore the dual clinical effects of reducing pain and muscle strength when the neuromodulation of the M1 with high-frequency rTMS combined with quadriceps strength training in KOA. In addition, to the best of our knowledge, this will be the first single-blind study on rTMS in KOA. Moreover, we will also analyze the correlation measurements between the primary outcomes (VAS, TQPEAK) and secondary outcomes (MEP, FC). Furthermore, the study’s exclusion criteria are relatively strict which will exclude many patients. In this case, it is possible to ensure that our experimental results have a certain degree of accuracy and validity.

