We recognize this study also has limitations. First, the blinding cannot be performed for the participants and the study operator, because of the visibility of the quadriceps strength training intervention, which might increase the risk of detection bias during the study’s implementation. Second, the exercise training in this protocol is only focuses on quadricep strengthening and not strengthening the whole kinetic chain. Although quadriceps weakness is closely related to the occurrence and development of KOA, strengthening the whole kinetic chain may have greater rehabilitation benefits for KOA than alone quadriceps strengthening. Third, account for the absence of direct evidence on rTMS for improve pain of KOA, we incorporated the effect size of rTMS in alleviating pian of the patients with fibromyalgia in sample size calculation [24]. While there are distinctions between the two types of disease, they both involve central sensitization.

In conclusion, the study will provide evidence to show whether there are synergistic effects following High-Frequency rTMS act on M1 combined with quadriceps strength training and clarify the mechanism of action. The study will help provide rehabilitation prescription recommendations for people with KOA.

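### The only analysis linking MEP and FC to pain and strength is a Pearson correlation with no arm term; pooled over four arms, it mixes treatment shifts with within-arm association

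*Protocol article*

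**What the plan says.** The Statistical analysis section gives the method: "Pearson correlation coefficient will be performed to detect the correlation between the primary outcomes (VAS, TQPEAK) and secondary outcomes (MEP, FC". The Discussion repeats it: "we will also analyze the correlation measurements between the primary outcomes (VAS, TQPEAK) and secondary outcomes (MEP, FC". Neither place says whether the coefficient is computed over all participants or within each arm, on raw values or changes, or at which visit. No partial correlation, arm-adjusted regression or mediation model is named.

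Continuous outcomes are otherwise compared by repeated-measures analysis of variance: "we will use the Two-way of variance with repeated measures; the Wilcoxon test will be used if not". The abstract says this tests group and time effects on the outcome measures, and it lists MEP and the MRI measures among the outcomes. So a randomised comparison of the mechanism variables is also planned.

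On design: "A total of 148 eligible participants will be assigned to four groups at a 1:1:1:1 ratio". Two arms (HT and HT + Q) receive active rTMS. Three (QT, ST + Q and HT + Q) receive quadriceps training. The article's conclusion says the study will show whether there are synergistic effects of rTMS "combined with quadriceps strength training and clarify the mechanism of action". The abstract and Background use the softer aim of exploring the mechanism.

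**The concern.** A mechanism claim needs to know whether patients whose excitability or connectivity changed more also had more relief or gained more strength. That is an association within arms. A Pearson coefficient over all arms also contains the covariance of the arm means. If rTMS moves MEP and, by any route, also moves VAS, the arm means line up and the coefficient departs from zero even if the two variables are unrelated among patients treated alike.

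The article's rationale is that rTMS acts on M1 and relieves pain, so such shifts are what the trial hopes to see. The analysis of variance can show that rTMS changes MEP, but it does not connect that change to pain or strength. The correlation is the only planned analysis that does, and at P < 0.05 it could be read as evidence of mechanism when it only restates that treatment affected both variables.

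**Working it through.** **The plan's own figure.** The article gives no figure for the correlation analysis, only the trial size: "ANOVA repeated measures between factor was chosen", with "effect size 0.24, alpha 0.05, power 0.80, number of groups 4, number of measures 6, and the sample size was calculated as 116". The correlation among repeated measures is not stated; 0.5 is assumed.

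- Noncentrality = f² × N × m / (1 + (m − 1)ρ) = 0.0576 × 116 × 6 / 3.5 = 11.45, with 3 and 112 degrees of freedom. Power is 0.806, so 116 reproduces. With ρ from 0.3 to 0.7, N would run from 84 to 148.
- Dropout: 29 / 0.8 = 36.25, hence 37 per arm and 148 in total.

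**Inputs to the check.**

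- Four equal arms in the order QT, HT, ST + Q, HT + Q; 37 per arm, or 29 as the number before the dropout allowance; two-sided alpha 0.05 (Statistical analysis).
- Within-arm SD 1 and within-arm correlation 0, so any significant result is a false positive for within-arm association.
- The article gives no effects on MEP, FC or TQPEAK, so the shifts d are assumptions. One anchor is f = 0.24: in a two-versus-two pattern the SD of the arm means is d/2, so d = 0.48. Applying it to MEP or FC as well is an assumption.
- VAS is scored as relief, so higher is better.

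**Formula.** Pooled r = cov(arm means) / √[(1 + var of x arm means)(1 + var of y arm means)].

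**Three arm patterns.** MEP always follows (0, d, 0, d), so its variance is d²/4.

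1. *VAS moved by rTMS only*, (0, d, 0, d). Covariance d²/4. At d = 0.8: 0.16 / 1.16 = 0.14.
2. *VAS moved equally by training and rTMS, additively*, (d, d, d, 2d). Covariance d²/8, VAS variance 3d²/16. At d = 0.8: 0.08 / √(1.16 × 1.12) = 0.07.
3. *TQPEAK moved by training only*, (d, 0, d, d). Covariance −d²/8, variance 3d²/16. At d = 0.8: r = −0.07.

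**False-positive rates** (simulation, at least 20,000 trials per scenario, 37 per arm):

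| Shift d | VAS, rTMS only | VAS, training = rTMS | TQPEAK, training only | Arm-adjusted |
|---|---|---|---|---|
| 0.48 SD | r 0.05, 10% | r 0.03, 6% | r −0.03, 6% | about 5% |
| 0.8 SD | r 0.14, 39% | r 0.07, 13% | r −0.07, 13% | about 5% |
| 1.0 SD | r 0.20, 70% | r 0.10, 24% | r −0.10, 24% | about 5% |

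With 29 per arm, the first pattern gives 9%, 32% and 59%. If training has twice the effect of rTMS on VAS, arm means (2d, d, 2d, 3d), the covariance is exactly 0 and the pooled test rejects in 4–5% of trials.

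**The case against.** **Pooling is inferred.** The article does not say that the coefficient is taken over all arms, and a condensed article may leave that to a fuller plan. This stands as a limit on certainty. It does not remove the point: the article does fix the method as a plain Pearson coefficient, which has no place for an arm term, and if within-arm coefficients are meant, one sentence settles it.

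**It is not the whole mechanism analysis.** A reader might infer that mechanism rests on a single correlation. It does not: VAS and TQPEAK against MEP and FC make at least four, and the analysis of variance compares the mechanism variables between arms. What stands is narrower: nothing else links the two sets of measures.

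**The large rates need a pattern the article does not expect.** The 39% and 70% assume that training does nothing for pain, whereas the Background and Discussion say quadriceps training relieves it. With an equal training effect they fall to 13% and 24%. This stands, so both sets must be shown.

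**The test is not wrong for marginal correlation.** When arms shift both variables, the marginal correlation really is non-zero, and the article states no rule for reading it as mediation. This is true; the error would lie in interpretation. But the stated purpose is mechanism, and the marginal coefficient does not answer that question.

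**Conclusion.** The point holds in a limited form. The only planned link between the mechanism measures and the clinical outcomes is unadjusted for arm and, on its natural reading, confounded by randomised treatment. At the article's one stated effect size the inflation is modest: about 10% instead of 5%, or 6% if training relieves pain equally. It becomes serious (39–70%) only with large, aligned shifts and no training effect on pain, and it vanishes under some patterns. For TQPEAK the spurious coefficient can be negative.

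A reader might infer that a false mechanism finding is likely whenever rTMS works on both variables. The documents do not support that: they give no effects on MEP, FC or TQPEAK, and the result depends on both the size and the pattern of the shifts. The conclusion rests on pooling over arms, on the assumed shifts and on zero within-arm correlation. The reason to change the method is that the adjusted test answers the intended question and holds its error rate in every scenario tried.

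**What to change.** Replace the plain Pearson correlation with an arm-adjusted (partial) correlation, or equivalently a regression of baseline-to-week-12 change in VAS or TQPEAK on change in MEP or FC, one value per participant, with arm as a covariate. Sex, age group and KL grade, the stratification factors, may be added. Report the coefficient as an association, not as proof of mechanism, and word the article's conclusion to match.

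The cost is a sentence or two and 3 degrees of freedom for arm, or about 6 with the three two-level stratification factors. No new data are needed: MRI is taken at baseline and after the 12-week intervention, and the abstract has all outcomes measured at baseline and week 12.

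While that sentence is open, reconcile its labels. It calls TQPEAK primary and MEP secondary, whereas the Outcomes sections list muscle strength as secondary and motor cortex excitability as primary for mechanism.
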